#### Maternal and Infant Outcomes

Prenatal, labor, and delivery data will be abstracted from the participant’s electronic medical record. Maternal and infant outcomes include: mode of delivery (vaginal or cesarean), adverse pregnancy outcomes (eg, diagnosis of gestational diabetes, insulin use, preeclampsia, depression, labor or delivery issues, and other complications), birth weight, length, sex, gestational age, date of birth, APGAR score, and any complications related to the infant during labor and delivery. In the event that labor or delivery data are missing or unavailable from the medical record, the investigators will obtain information from the participant’s self-report.

### Implementation Marker Procedures

Our team has ample experience with evaluating program implementation [96-98,129-133], including in the HMZ proof-of-concept study [42] and feasibility trial [19]. The Quality Implementation Framework [49] and Quality Implementation Tool [50] will guide examination of the following markers:

Subject engagement and participation: Fidelity monitoring evaluations are conducted for each subject and staff after each session. A trained staff observer reviews video recordings of 50% of intervention and attention control sessions and follows a review checklist to measure engagement (degree of subject responsiveness with content, discussion, and activities) [134,135].Subject acceptability: Subjects and staff complete weekly checklists to assess attendance (0%-100% attendance at pre- and postintervention assessments; 0%-100% attendance at intervention and attention control sessions), compliance (0%-100% compliance with mHealth tools and surveys during free-living pre- and postintervention sessions and over the course of the study for all subjects; 0%-100% compliance with attention control or HMZ 2.0 activities), and quality and completeness of data (0%-100% of usable data for each subject).Dosage exposure is assessed by (1) weekly checklists completed by subjects or staff regarding the amount of program content delivered or received (goal 85%+ coverage) [19]; (2) fidelity monitoring by a trained staff observer who reviews video recordings from the same sample of 50% of video recordings noted above; and (3) tracking of the number of dosage changes determined by the model-based control system, number of days between dosage change recommendation and implementation by staff, and number and type of PA or EI strategies suggested or used.Staff engagement: Fidelity monitoring is conducted by a trained staff observer who reviews video recordings from the same sample of 50% of video recordings noted above and follows a checklist to measure engagement (enthusiasm, preparedness, session delivery effectiveness, and responsiveness to the subject).Staff burden: Weekly checklists are completed by staff for the amount of time spent preparing for sessions, responding to or following up with subjects, and using the HMZ 2.0 digital platform, and for issues with delivering dosage recommendations to the subjects.Study delivery costs: A trained staff member tracks and calculates the time and financial costs of the study. Postintervention semistructured interviews with HMZ 2.0 subjects elicit key facilitators and barriers to study participation. The interview guide has been developed with standard procedures [136,137] from our past studies [10,19,42-45,107,138-140]. Expert feedback will be obtained from key clinician stakeholders (ie, registered dietitians, nurses, obstetrics or gynecology providers, etc) on the strengths and limitations of using the HMZ 2.0 digital platform, potential barriers to scaling-up use in prenatal care (eg, clinician beliefs about technology and connectivity issues), and suggestions for improvements. This valuable feedback will be used to make additional refinements to HMZ 2.0 to scale-up future use by prenatal care clinicians.

### Statistical Analysis

For study aims 1 and 2, time series methodology will be used on a subject basis (ie, cubic polynomial spline 3-lag auto-regressive models with maximum likelihood as the estimation method) followed by a fixed effects meta-analytic approach to combine information in order to compare the intervention group to the control group [141-143]. Mixed effects models will be used when the meta-analytic approach does not fit the data [56,62-65]. Potential confounding variables (eg, maternal age, parity, and income; infant sex; and adverse maternal-infant outcomes) [6,144] will be included in the models as covariates when appropriate. We will explore the extent to which prenatal sleep and eating behaviors impact postintervention GWG, PA, or EI and infant birth weight to inform modifications to the maternal energy balance and infant birth weight models. The intent-to-treat principle will be followed. Our statistical approach is robust if data are missing at random (multiple imputation will be considered if missing data are problematic) [145]. Hypothesis tests will invoke a 2-sided significance level of .05. Analyses for the synthesis of mHealth data and the predictive control system are informed by MATLAB toolkits and past experience [51,146,147]. Model personalization will use control-theory models, and requisite computations will be performed for optimal dosage changes [112,113,128,148-150]. For study aim 3, descriptive statistics will be used to examine the percentage and frequency for implementation markers. Formative methods will be used to organize, code, and rank order interview data [136,137]. Study findings will be used to further optimize HMZ 2.0 for effectiveness and scalability. Data will be collected and stored in REDCap [88]. Deidentified data will be exported from REDCap [88] to statistical packages. Subject confidentiality will be maintained with subject IDs. Data security is ensured with Penn State standard procedures.

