## Introduction

### Background

High maternal prepregnancy BMI and high gestational weight gain (GWG) elevate the risks for poor pregnancy outcomes (eg, gestational diabetes and hypertension) and fetal outcomes (eg, large for gestational age birth weight) [1-6]. High BMI and GWG may also “program” the child’s metabolism for life [7,8] and increase the future risks for obesity and type 2 diabetes in both mothers and their offspring [1-6]. As such, managing GWG has high clinical and public health significance, and it can improve maternal health and impact the etiology of obesity or diabetes in offspring at a crucial time in the life cycle [1-6,8].

Guidelines from the Institutes of Medicine (IOM) [1] and National Academy of Medicine [2] recommend that the optimal total GWG should be based on a woman’s prepregnancy BMI category (ie, overweight: 6.8-11.3 kg; obese: 5.0-9.1 kg). However, evidence from a meta-analytic review including over 1 million pregnant women found that nearly 50% of women exceeded their recommended goals [9], and this was prevalent among those with normal weight as well as those with overweight or obesity. Furthermore, data from a meta-analysis of almost 200,000 women from 25 international cohort studies in the LifeCycle Project [6] showed the highest risk for adverse outcomes among women with both high BMI and high GWG. Given these concerns as well as the rapidly changing landscape of health care delivery since the COVID-19 pandemic, there is a critical and timely need for scalable approaches to effectively regulate GWG. One such strategy that may reach more pregnant women and reduce the burden on prenatal clinicians who monitor GWG is an automated approach that relies on a digital platform with remote delivery and passive remote data collection to monitor and effectively and efficiently regulate GWG.

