### Goal of This Study

The goal of this study is to describe the protocol for a randomized controlled optimization trial to examine the efficacy of the enhanced HMZ 2.0 intervention with the new automated control system and digital platform to regulate GWG and influence secondary maternal and infant outcomes while collecting implementation data to inform future scalability. Aim 1 is to examine the efficacy of the intervention in terms of GWG (primary outcome) and maternal PA and EI behaviors and social cognitive determinants on comparing intervention and control groups. It is hypothesized that the intervention group will (1) have lower pre- to postintervention GWG and be more likely than controls to achieve GWG within the guidelines [1,2], and (2) have higher PA kcal (and total kcal) and PA or EI determinants and lower EI kcal than controls. Aim 2a is to measure pre- to postintervention differences in secondary maternal sleep and eating behaviors. It is hypothesized that the intervention group will have fewer nighttime awakenings and less uncontrolled eating than controls. Aim 2b is to examine the impact of the intervention on birth weight and adverse pregnancy, labor, and delivery outcomes. It is hypothesized that the intervention group will show lower birth weight adjusted for gestational age and will have lower occurrences of adverse pregnancy, labor, and delivery outcomes than controls. Aim 3 is to examine the impact of implementation markers on intervention efficacy in terms of GWG and secondary outcomes. It is hypothesized that subject engagement, acceptability, dosage exposure, and staff burden or acceptability will moderate the effect of the intervention on study outcomes. This information will inform how to scale-up the HMZ 2.0 intervention for future use by prenatal clinicians.

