### Randomization Procedures

A trained staff member randomizes each participant after the preintervention measures via a randomization module in REDCap [88]. The study’s biostatistician has developed the randomization scheme using variable-size random permuted blocks to ensure the number of subjects in each group is balanced after each set of *B* randomized subjects, where *B* is block size. The biostatistician programs the REDCap module, and the remaining study staff do not have access to the randomization scheme. Randomization to control (n=72) and intervention (n=72) groups uses 1:1 allocation; subjects are entered consecutively. Randomization is stratified by prepregnancy BMI status (<29.9 vs ≥30 kg/m^2^). A staff member calls each woman to inform her of study assignment. She is then provided with study information and education materials for her group assignment. The investigator is blinded to intervention assignments.

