	**Maternal-infant labor or delivery and adverse pregnancy outcomes**			
		Diagnoses of gestational diabetes, insulin use, preeclampsia, and depression	Postintervention only (at delivery)	
		Labor or delivery issues and other complications	Postintervention only (at delivery)	
		Infant APGAR score and mode of delivery (vaginal or cesarean)	Postintervention only (at delivery)	

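### Adverse maternal-infant outcomes, which arise after randomisation and are Aim 2b endpoints, are listed as possible covariates in the Aim 1 and 2 arm comparisons

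*Protocol article*

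**What the plan says.** The Statistical Analysis section covers Aims 1 and 2 together, and so includes the primary GWG comparison. Its covariate sentence opens "Potential confounding variables (eg, maternal age, parity, and income" and ends "infant sex; and adverse maternal-infant outcomes) [6,144] will be included in the models as covariates when appropriate". The same paragraph commits to intention to treat.

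Four other places show what these covariates are:

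- **Endpoint status.** Under Goal of This Study, Aim 2b hypothesises that the intervention group "will have lower occurrences of adverse pregnancy, labor, and delivery outcomes than controls".
- **Content and timing.** Table 1 lists "Diagnoses of gestational diabetes, insulin use, preeclampsia, and depression", together with labour and delivery complications, as collected at delivery only.
- **Causal position.** The Background states that high prepregnancy BMI and "high gestational weight gain (GWG) elevate the risks for poor pregnancy outcomes (eg, gestational diabetes and hypertension".
- **Randomisation.** Under Randomization Procedures, "A trained staff member randomizes each participant after the preintervention measures", which places allocation before anything recorded at delivery.

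On the strata, the same section says "Randomization is stratified by prepregnancy BMI status (<29.9 vs ≥30 kg/m^2", and the abstract gives the same cut-points. Eligibility runs from BMI 24 to 45.

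**The concern.** A confounder of a treatment comparison must influence both allocation and outcome. Randomisation removes any influence on allocation, so the usual reason to adjust is to gain precision from baseline variables. An event that follows randomisation and may be altered by treatment does not qualify.

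Two kinds of harm follow. For GWG, an adverse outcome lies downstream of the response. Comparing arms among women with the same adverse-outcome status makes their weight gains more alike and pulls the estimated effect toward zero. For birth weight, an adverse outcome can lie on the path from intervention to infant, so adjusting removes part of the effect that Aim 2b sets out to measure. If an adverse outcome such as gestational diabetes instead changes later weight gain, it is a mediator for GWG as well, and still not a confounder.

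The trial has little room for attenuation. It is powered for 2.9 kg, its feasibility study found 1.9 kg, and the Limitations section concedes that it may be underpowered.

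**Working it through.** **1. The plan's own power figure.** Inputs from Power Calculations: 72 per arm, 10% dropout, SD 5.7 kg, difference 2.9 kg, two-sided .05.

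- Completers per arm: 72 × 0.9 = 64.8, or 64 rounded down.
- SE = 5.7 × √(2/64) = 1.008 kg. Noncentrality = 2.9 / 1.008 = 2.88.
- Power from the noncentral t distribution: 81.5% with 64 per arm, 82.0% with 64.8.

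The stated 80% reproduces and is slightly conservative. This point does not alter it.

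**2. The covariate set against the article's own statements.**

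| Property of a legitimate covariate | Adverse maternal-infant outcomes in this article |
|---|---|
| Fixed before randomisation | No: recorded at delivery (Table 1) |
| Not affected by treatment | Expected to fall under the intervention (Aim 2b) |
| Not a consequence of the response | High GWG raises the risk (Background) |

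Infant sex, in the same list, is fixed at conception and cannot be affected by treatment. It raises no such problem.

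**3. Size for GWG, finite sample.** Ordinary least squares, 65 per arm, SD 5.7 kg, true effect −2.9 kg, 4,000 runs per scenario. The link (log-odds of an adverse outcome per SD of GWG) and an intercept giving roughly 30% adverse outcomes are assumptions; the article gives neither.

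| Link | Unadjusted estimate | Adjusted estimate | Shrinkage | Power, unadjusted → adjusted |
|---|---|---|---|---|
| 0.5 | −2.901 | −2.765 | 1 − 2.765/2.901 = 4.7% | 82% → 79% |
| 1.0 | −2.882 | −2.460 | 1 − 2.460/2.882 = 14.6% | 82% → 75% |
| 1.5 | −2.915 | −2.196 | 1 − 2.196/2.915 = 24.7% | 82% → 70% |

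**4. Size for GWG, large sample with weaker links.** Assumed odds ratios of 1.3 to 2.0 per 5 kg, prevalence 24% to 29%. On the scale of step 3, these are ln(1.3) × 5.7/5 = 0.30 and ln(2.0) × 5.7/5 = 0.79 per SD. Shrinkage is 2% to 11%, to about −2.6 kg at worst. This agrees with step 3, where a link of 0.5 gives about 5% and 1.0 about 15%.

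**5. Size for birth weight.** Adding assumed effects of 20 g per kg of GWG and 150 g per adverse outcome, the arm effect shrinks by 8% to 23%. Both effects, and the positive sign of the second, are assumptions.

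**6. No true GWG effect.** Suppose the intervention lowers adverse outcomes by a route other than GWG (log OR −0.7, link 1.0). The adjusted model then gives +0.59 kg with type I error 9.7%, against 5.1% unadjusted. With log OR −0.5 to −1.0 under the assumptions of step 4, the false difference is +0.34 to +0.65 kg. The positive sign means more weight gain in the intervention arm.

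**7. BMI stratum and cut-points.**

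- If the stratum were left out of the model, with an assumed 2.2 kg difference between strata, the SE would be 1.017 instead of 0.998. That is 1.9% larger, with no bias and type I error of 5.0% against 5.4% (simulation noise is about 0.3 points).
- The printed strata leave a gap of 0.1 BMI unit. If BMI were uniform over 24 to 45, it would hold 0.1/21 × 144 = 0.7 women. If BMI follows a truncated normal (mean 29 to 31, SD 4 to 5), it holds 0.9% to 1.1%, or 1.3 to 1.6 of 144.

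**The case against.** The strongest reply is that the sentence is conditional. It speaks of potential confounders, gives examples, applies them only where suitable, and spans every Aim 1 and 2 outcome from GWG to delivery events. It does not assign adverse outcomes to the primary GWG model, and a full analysis plan may settle the matter. This has force against saying that the primary analysis will adjust for them. It does not remove the defect. The article names these variables as confounders for the arm comparisons and gives no rule to keep them out of any one. The problem is what the list includes, not detail left to another document.

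The size is also open to challenge. Every link strength is assumed, the 25% figure needs the strongest one, and the false difference in step 6 needs a treatment effect on complications that bypasses GWG. All of that stands. A reader might infer from step 6 that the adjustment could manufacture evidence of benefit. In the scenarios examined, the false difference runs against the intervention.

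A reader might also infer that the stratification factor will be left out, since BMI status is not named. The article does not support this: the list is only of examples and nothing in it excludes BMI stratum. Omission would in any case cost a little precision and cause no bias.

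Finally, the gap in the strata looks like a slip of notation, because weight-gain targets are set by overweight versus obese. That is probably right. The article does not show which cut-point the REDCap module uses.

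**Conclusion.** The point holds for adverse maternal-infant outcomes as covariates. By the article's own account they follow randomisation, are endpoints, and lie downstream of GWG, so conditioning on them can bias the randomised comparison. The direction for GWG is toward zero when the intervention acts through weight gain. The amount, about 2% to 25% for GWG and 8% to 23% for birth weight, is illustrative and rests wholly on assumed links, prevalence and birth-weight effects. The reasoning about the covariates does not depend on those figures.

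The gap in the BMI strata is real but minor. It concerns about one or two women and biases nothing.

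**What to change.** In Statistical Analysis, delete adverse maternal-infant outcomes from the covariates of all arm comparisons. State that covariates in those models are limited to variables fixed before randomisation. The BMI stratum used in randomisation can be among them, and infant sex may stay. State that adverse outcomes are analysed only as outcomes, or in models labelled exploratory that carry no claim about the randomised effect.

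Separately, in the abstract and Randomization Procedures, state the BMI cut-point actually programmed in REDCap, presumably <30 vs ≥30 kg/m². If the module does contain the gap, record how any woman falling in it was assigned.

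Both are changes of wording plus one check of the randomisation module. Neither needs new data or alters the sample size. Data collection is expected to run to December 2027, so the covariate rule can be fixed well before analysis.

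### Aim 3 states a moderation hypothesis but is given only descriptive marker summaries, and the first-line model for Aim 2b cannot be fitted to outcomes recorded once at delivery

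*Protocol article*

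**What the plan says.** **Aim 3.** The Goal of This Study section of the protocol article states the purpose: "Aim 3 is to examine the impact of implementation markers on intervention efficacy in terms of GWG and secondary outcomes". The hypothesis attached to it is that a set of markers, among them "dosage exposure, and staff burden or acceptability will moderate the effect of the intervention on study outcomes". The Statistical Analysis section then gives the quantitative method: "For study aim 3, descriptive statistics will be used to examine the percentage and frequency for implementation markers". The only other Aim 3 method named there is qualitative coding and ranking of interview data.

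**Markers.** Implementation Marker Procedures defines them. Attendance and compliance are recorded as percentages in both arms. Dosage exposure includes "tracking of the number of dosage changes determined by the model-based control system" and the delay until staff act on a recommendation.

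**Aim 2b.** The hypothesis, with the control arm as comparator, reads: "the intervention group will show lower birth weight adjusted for gestational age and will have lower occurrences of adverse pregnancy, labor, and delivery outcomes". Table 1 gives the timing of the maternal and delivery outcomes as "Postintervention only (at delivery"), and gives birth weight the same timing. The Statistical Analysis section says: "For study aims 1 and 2, time series methodology will be used on a subject basis". It specifies cubic spline models with three autoregressive lags, followed by a fixed effects meta-analysis of the subject-level results. Mixed effects models, with covariates where appropriate, are the fallback if the meta-analytic route does not fit.

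**The concern.** In both places the stated method does not answer the stated hypothesis.

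For Aim 3, moderation means that the difference between arms in an outcome changes with the level of a marker. Describing how often a marker occurs says nothing about that. An analyst who follows the text can report delivery and uptake but has no evidence for or against the hypothesis. The article says this aim will inform scale-up, so readers may take a descriptive summary for a tested claim.

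For Aim 2b, the first-line method presupposes a series of measurements on each woman. Birth weight, mode of delivery and pregnancy diagnoses come once. An analyst who follows the text cannot start, and must choose a model after the fact for outcomes that carry directional hypotheses.

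**Working it through.** The plan gives no figure for either point. Its only power statement concerns the primary outcome. The check therefore sets hypothesis against method, with one parameter count.

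**Aim 3: what moderation needs and what is named**

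1. Required: a model of the form outcome = a + b·arm + c·marker + d·(arm × marker), with d as the quantity of interest.
2. Named: percentage and frequency of the marker. This contains no outcome, no arm contrast and no d.
3. Could another named method fill the gap? The time-series and mixed models are introduced for Aims 1 and 2 only. The abstract's list (descriptive statistics, time series with meta-analysis, mixed effects models) adds nothing for Aim 3.
4. Could every marker enter such a model? The count of controller-determined dosage changes and the delay to implementation have no counterpart in the control arm. With no control values, d is undefined for them. Attendance and compliance exist in both arms, so d can be written down for those.

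**Aim 2b: parameters against observations**

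- Cubic trend: 4 coefficients. Lags: 3. Residual variance: 1. Total 4 + 3 + 1 = 8, before any spline knot.
- Observations per woman: 1 (Table 1).
- A 3-lag model needs more than three time points before it has one usable row. A trial fit of a 3-lag model to a single value was refused by the software, so there is no subject-level estimate to pool.

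**Aim 2b: the fallback**

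With one value per woman, a random intercept and the residual cannot be separated, because only their sum is identified. This was checked on simulated birth weights (assumptions: 65 women per arm, control mean 3400 g, true difference −150 g, SD 500 g):

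| | Random-intercept model | Ordinary regression |
|---|---|---|
| Arm difference (g) | −146.3 | −146.3 |
| Standard error (g) | 45.5 | 80.1 |
| Variance | 104,383 + 104,383 | 208,766 |

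The ordinary standard error checks by hand: √(208,766 × 2/65) = 80.1. The mixed model halved the variance arbitrarily, gave no standard error for the random-effect variance, and returned a wrong standard error for the arm effect. The value 45.5 is one program's output and not a general result. The general point is that the arm effect is estimable, but its precision can be trusted only once the random effect is removed. What remains is ordinary covariate-adjusted regression.

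**Caveat on size, for an Aim 3 interaction on weight gain**

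This is an illustration and not part of the defect. The inputs from Power Calculations are SD 5.7 kg and 10% dropout, so 72 × 0.9 = 64.8, about 65 per arm. On these inputs a two-sample t-test has 82.1% power for 2.9 kg, in line with the plan's 80%. Assume a two-level marker with proportion p at one level, the same in both arms:

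SE(d) = 5.7 × √[2/(65p) + 2/(65(1 − p))], and the detectable d at 80% power is 2.80 × SE(d).

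- p = 0.5: SE 2.00, detectable d 5.6 kg
- p = 0.3: SE 2.18, detectable d 6.1 kg
- p = 0.2: SE 2.50, detectable d 7.0 kg

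**The case against.** The best defence is that this is a journal article. Models for individual secondary outcomes are commonly left to a full protocol or analysis plan, and one sentence covering two aims is condensed prose. That stands in part: the absence of a named binary-outcome model would not be a finding by itself. It does not rescue the two stated assignments. The article does not leave Aim 3 open; it names a method that cannot address the hypothesis. Nor does it leave Aim 2b open; it assigns a first-line method with no exception for outcomes measured once.

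Stronger readings are tempting, and the document does not support them:

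- **Aim 2b has no runnable analysis.** A reader might infer this from the parameter count. The mixed-effects fallback is named for the same aims, however, and without its random effect it becomes a regression that can test the birth-weight hypothesis.
- **The article claims to test moderation with percentages.** It does not. It summarises the markers and names no moderation model.
- **Monthly scales are too short for a 3-lag model.** This would concern Aim 2a, whose hypotheses are on nighttime awakenings, recorded daily, and uncontrolled eating. The eating questionnaire is weekly in the open-loop phase and monthly afterwards.
- **The dose-outcome analysis is confounded by predicted weight gain.** No such analysis is proposed. The point is only a warning against adding one: according to the Figure 4 caption, dosages 3 to 5 depend on controller decisions.
- **Aim 3 is underpowered.** The 5.6 to 7.0 kg range rests on an assumed dichotomy of markers that are recorded as percentages. It is a reason to label any interaction exploratory and not an error in the plan.

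**Conclusion.** The concern holds in two limited parts.

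For Aim 3, the hypothesis and the analysis contradict each other within the article. The one quantitative method named can test none of the hypothesised moderators, and for the intervention-only dosage markers no arm-by-marker interaction exists to be tested. This rests on reading "will moderate the effect of the intervention on study outcomes" in its usual sense of effect modification.

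For Aim 2b, the first-line method cannot be fitted (1 observation against at least 8 parameters). The fallback is usable only in a reduced form that the text does not state. This rests on Table 1's timing and on the Aims 1 and 2 sentence covering Aim 2b, since it carves nothing out.

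Only secondary aims are affected. The primary weight-gain comparison and its sample size are untouched. The change should be made, and it is easy now: the article reports 12 women enrolled of 144 planned.

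**What to change.** **Aim 3.** Choose one of two routes and make the aim and the analysis agree.

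- Restate the aim as descriptive and remove the moderation hypothesis.
- Or keep moderation as exploratory, limited to arm-by-marker interactions for markers measured in both arms, such as attendance and compliance. Report estimates with confidence intervals. These markers arise after randomisation and refer to different sessions in each arm, which is a further reason for the exploratory label.

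Under either route, report intervention-only markers descriptively and make no causal dose-response claim from them.

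**Aim 2b.** Exempt the delivery outcomes from the time-series sentence. Name linear regression for birth weight adjusted for gestational age, and logistic or modified Poisson regression for binary outcomes, each comparing arms and adjusting for the BMI stratum used in randomisation.

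**Cost.** A few sentences in the aims and the analysis section, and no new data. The price is a weaker claim for Aim 3.
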